### Outcome measurement

2.7.

#### Primary outcome

2.7.1.

Perioperative cumulative hypothermia effect value (*Σ Δ*T_i_ × *Δ*t_i_, i = 1…, *n*).

Note: When the body temperature at a certain time (i) is <36°C, hypothermia variation will be recorded as *Δ*T_i,_ (*Δ* T_i _= 36°C-T_i_), and the duration of this hypothermia variation will be recorded as *Δ*t_i_.

#### Secondary outcomes

2.7.2.

(1)Cumulative hypothermia effect value (*Σ Δ*T_i_ × *Δ*t_i_, i = 1…, *n*) in the preoperative waiting room, operating room, and PACU;(2)Difference value between intraoperative core temperature and axillary temperature;(3)Results of arterial blood gas analysis in the anaesthesia recovery period, including pH, lactic acid, and haemoglobin values;(4)Shivering score, Cornell Assessment of Pediatric Delirium score, and thermal comfort score in the anaesthesia recovery period;(5)Body temperature in the morning of the first day after surgery;(6)The incidence of incision infection during hospitalization;(7)The morbidity of major complications during postoperative hospitalization;(8)Length of stay and expenses;(9)All-cause mortality 30 days after the operation.

Note: a. Anaesthesia recovery period refers to the time from stopping anaesthetic infusion to the time when the children are completely conscious and fully awake. b. Major complications during postoperative hospitalization include postoperative pulmonary complications, arrhythmias requiring treatment, myocardial infarction, sepsis, renal failure, central nervous system events, anastomotic leakage, and accidental transfer to the intensive care unit.

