## Introduction

1.

Constant core body temperature is a necessary condition to ensure basic metabolism and vital activity, and normal core body temperature is generally between 36.5°C and 37.5°C (1, 2). A perioperative core body temperature lower than 36.0°C is defined as inadvertent perioperative hypothermia (IPH) (3). The incidence of IPH in adults is approximately 50% to 90% (4). IPH can contribute to a variety of perioperative complications (5), such as cardiovascular accidents (6, 7), increased bleeding (8, 9), surgical incision infection (10), delayed recovery (11), internal environment disturbance (12), and prolonged length of stay. Young age is an important risk factor for IPH (13, 14). The special physiological characteristics of children determine that their body temperature is more susceptible to environmental changes (15). Without proper warming measures, the incidence of IPH could be higher than that in adults. The thermoregulation system of children is not mature, including limited hair, less subcutaneous fat, and a greater overall surface area to body weight ratio, and the ATP-based independent thermoregulation mechanism has not been fully established, leading to insufficient heat production and excessive heat dissipation (5, 16). This relationship is especially true for infants, who generate heat through brown adipose tissue metabolism instead of shivering in low-temperature environments. This metabolism is innervated by sympathetic nerves and inhibited during general anaesthesia, further increasing the risk of IPH (17–19). Therefore, it is imperative to undertake appropriate warming measures for children during the perioperative period.

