#### Exclusion criteria

2.3.2.

(1)Abnormal body temperature caused by diseases or medicines before surgery;(2)Elective surgery requiring controlled hypothermia;(3)Children with a definite history of cardiac insufficiency or congenital heart disease;(4)Children with a definite history of metabolic diseases, such as thyroid dysfunction and diabetes;(5)Changes in laboratory examination of routine blood, blood biochemistry, and blood clotting exceeding 1.5 times the normal value;(6)The tracheal tube expected to be retained after the operation;(7)Postoperative thermoregulation expected to be affected, such as the neurosurgery in the vicinity of the hypothalamic thermoregulatory centre; and(8)Unwillingness to participate in this trial or participate in other clinical trials.

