### Standardized anaesthesia management

2.6.

All eligible children will receive standardized anaesthesia management procedures. Except for real-time axillary temperature monitoring, when the children enter the operating room, standard monitoring will be applied, including noninvasive blood pressure, heart rate, and pulse oximetry saturation. Invasive arterial pressure, end-tidal carbon dioxide partial pressure, anaesthesia gas monitoring, and the nasopharyngeal core temperature will be monitored after anaesthesia induction. Before anaesthesia induction, the anaesthesiologist in charge intravenously will administer midazolam (0.025–0.075 mg·kg^−1^). General anaesthesia will be induced with sufentanil 0.5 μg·kg^−1^, propofol 2–3 mg·kg^−1^, and cis-atracurium 0.1–0.2 mg·kg^−1^ or rocuronium 0.4–0.6 mg·kg^−1^. After intubation, mechanical ventilation will be set in the volume-controlled mode. The tidal volume will be 8–10 ml·kg^−1^ and the respiratory rate will be 14–20 breaths per minute. Remifentanil (0.1–0.2 μg·kg^−1^·min^−1^) and propofol (8–10 mg·kg^−1^·h^−1^) will be used to maintain the total intravenous infusion anaesthesia and adjusted for sedative and analgesic needs during the operation. Corresponding treatment will be administered according to the children's status to maintain the mean arterial pressure and heart rate within 30% of the baseline values intraoperatively. The infusion of propofol and remifentanil will be stopped at the end of surgery. After extubation, children will be transferred to the PACU and further transferred to the inpatient ward or intensive care unit based on their condition.

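### Recovery haemoglobin is compared without the preoperative value that screening implies is on file, which costs precision but not validity; pH alone is a weak metabolic marker in a window that can span extubation

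*Protocol article*

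**What the plan says.** **Outcome.** Section 2.7.2, item (3), of the protocol article is "Results of arterial blood gas analysis in the anaesthesia recovery period, including pH, lactic acid, and haemoglobin values". Note a to that section defines the window: "Anaesthesia recovery period refers to the time from stopping anaesthetic infusion to the time when the children are completely conscious and fully awake".

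**Anaesthesia.** Section 2.6 places that window in the course of care. During surgery, "After intubation, mechanical ventilation will be set in the volume-controlled mode". Then "The infusion of propofol and remifentanil will be stopped at the end of surgery", and "After extubation, children will be transferred to the PACU".

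**Preoperative blood tests.** Exclusion criterion (5) in section 2.3.2 is "Changes in laboratory examination of routine blood, blood biochemistry, and blood clotting exceeding 1.5 times the normal value". It cannot be applied without a preoperative blood count. Section 2.7.3 does not name haemoglobin among the baseline data, although its list is not exhaustive.

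**Analysis.** Section 2.11 assigns normally distributed continuous variables to Student's t test and other continuous variables to the Kruskal-Wallis test. It mentions no baseline covariate for any outcome.

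**The concern.** Children aged 1 to 12 years from several surgical specialties can be expected to differ in haemoglobin before any treatment. A single value after surgery carries all of that variation into the comparison of arms. If warming affects blood loss, which the introduction gives as a reason to avoid hypothermia, a real difference in haemoglobin could be missed for want of a covariate that should already be in the notes.

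The second matter is how to read pH. The window opens when the infusions stop in a ventilated child and closes when the child is awake, so extubation can fall inside it. The text ties the sample to no event within the window. PaCO2 can change when the mode of breathing changes, and pH follows it. The introduction names disturbance of the internal environment as a harm of hypothermia, and pH alone cannot say whether a change is metabolic or respiratory.

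**Working it through.** The plan states no figure on this point, so there is nothing to reproduce. The checks below use its sample size and otherwise rest on labelled assumptions.

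**Inputs from the protocol article.** Sample size 400, allocation 1:1 and dropout 20% (sections 2.5 and 2.8). Evaluable children per arm: 400 × 0.8 / 2 = 160.

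**Inputs assumed.** Correlation r between preoperative and recovery haemoglobin, 0.3 to 0.8; a true haemoglobin difference of 0.3 SD; two-sided α of 0.05; and the pH and PaCO2 values given below.

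**1. Is the unadjusted haemoglobin comparison valid?** With random allocation and no true effect, 5,000 simulated trials at 160 per arm gave a mean bias of about 0. The t test had a false-positive rate of 5.3% (r = 0.5) and 4.8% (r = 0.7) at a nominal 5%. It is valid.

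**2. What does adjustment gain?** Residual variance as a fraction of the unadjusted variance is 1 − r². Power is approximately Φ(0.3 / √((1 − r²) × 2/160) − 1.96). Unadjusted: 0.3 / 0.1118 = 2.68, and Φ(2.68 − 1.96) = 77%.

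| Assumed r | Variance removed | Variance left | Power for 0.3 SD |
|---|---|---|---|
| none (unadjusted) | 0% | 1.00 | 77% |
| 0.3 | 9% | 0.91 | 80% |
| 0.5 | 25% | 0.75 | 87% |
| 0.7 | 49% | 0.51 | 96% |
| 0.8 | 64% | 0.36 | 99% |

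**3. Can pH separate respiratory from metabolic change?** By the Henderson-Hasselbalch relation, the change in pH is log10(ratio of bicarbonate) − log10(ratio of PaCO2). With illustrative values:

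- PaCO2 40 to 50 mmHg, bicarbonate fixed: log10(40/50) = −0.097
- the same, with bicarbonate rising from 24 to 25 mmol/L: log10((25/24) × (40/50)) = −0.079
- PaCO2 40 to 45 mmHg, bicarbonate fixed: log10(40/45) = −0.051
- bicarbonate 24 to 22 mmol/L, PaCO2 fixed: log10(22/24) = −0.038
- bicarbonate 24 to 20 mmol/L, PaCO2 fixed: log10(20/24) = −0.079

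At fixed bicarbonate, the respiratory change ranges from 0.051/0.079 = 0.65 times to 0.097/0.038 = 2.6 times the metabolic one. Which dominates depends on the values chosen. The two are of similar order, and pH alone does not tell them apart.

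**4. Does a floating sampling time bias pH?** Assume an SD of 0.04 and that spontaneous breathing lowers pH by 0.03, 0.05 or 0.08. Each setting used 4,000 simulated trials at 160 per arm with no true effect of warming.

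| Share sampled during spontaneous breathing | Difference between arms | False-positive rate |
|---|---|---|
| 50% and 50% | 0 | 4.4% to 4.8% |
| 60% and 40% | 0.006, 0.010, 0.016 | 23%, 48%, 72% |

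With equal timing the only cost is spread: at a 50:50 mix the SD rises from 0.040 to between 0.043 and 0.057. Bias needs timing that differs between arms.

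**The case against.** A reader might infer that neither haemoglobin nor pH can isolate an effect of warming. The documents do not support that.

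- **Haemoglobin.** Randomisation within centre makes the post-surgery comparison unbiased, as step 1 shows. Only precision is lost. The choice of covariates is often left to an analysis plan, and none is shown. That is fair, but section 2.11 does state a test, and that test is unadjusted, so recommending a better one is within bounds.
- **pH timing.** The claim that a pH result would reflect sampling time rather than temperature is conditional. It needs timing to differ by arm. That is possible: the introduction says that hypothermia delays recovery, and the anaesthesiologists in charge are unblinded. But the 60/40 split is assumed, both arms share one anaesthetic regimen, and the text does not say who draws the sample. If cold itself delays recovery, part of any resulting pH difference is a consequence of temperature. The study schedule (Figure 1, not shown) or the full protocol may also fix the time. This objection stands, so the missing time point is no error in itself.
- **Markers.** The outcome list is open-ended and already names lactate, a metabolic marker. Base excess and PaCO2 are not ruled out. This also stands: the plan does not leave metabolic change unmeasured, but it does not name the measures that would make pH interpretable.
- **Choice of sampling event.** A common event has a price. A sample when the infusions stop would miss any effect of warming in the PACU, and any lactate produced by shivering later in recovery. A later sample moves further into the period when breathing mode varies.

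**Conclusion.** The point holds as a low-cost improvement of minor severity. It concerns one of nine secondary items and does not touch the primary outcome or the sample size.

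For haemoglobin, the stated analysis is valid but inefficient. The loss is about r² of the variance, 9% to 64% over the assumed range of r. The documents give no correlation, and at the low end the gain is small. The conclusion also assumes that the screening haemoglobin is retrievable for each child, which exclusion criterion (5) implies but section 2.7.3 does not state.

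For pH, the wording supports two limited statements: the defined window can include two breathing states, and pH by itself mixes respiratory and metabolic change. Bias is a possibility that depends on timing differing between arms. It is not an established consequence of the plan.

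**What to change.** **Haemoglobin.** Add the preoperative haemoglobin from the screening blood count to the recorded baseline data. Analyse recovery haemoglobin by ANCOVA with that value as covariate. ANCOVA is preferable to a change score because the covariate and the outcome may come from different analysers. Cost: one field on the case report form and one sentence in section 2.11.

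**Blood gas.** Report base excess and PaCO2 from the same sample alongside lactate. Name base excess as the metabolic marker and keep pH as descriptive. Record whether the child was ventilated or breathing spontaneously at sampling, and the time since the infusions stopped. These arise after randomisation, so use them to describe the arms and to check for a difference in timing, not as routine adjustment covariates. No extra blood is needed.

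**Sampling event.** If the study schedule does not already do so, name one event common to both arms and give the reason for choosing it, given the trade-off between a uniform breathing state and capturing later effects of warming. The cost is wording and site compliance.

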**Methods:**

This study is a multicentre, prospective, randomized controlled trial. From August 2022 to July 2024, 400 paediatric patients undergoing elective surgery will be recruited in four centres and randomly divided into the active warming strategies group and control group at a ratio of 1:1. The primary outcome is the perioperative cumulative hypothermia effect value (*Σ Δ*Ti × *Δ*ti, i = 1…, *n*). Multiple complications covering the anaesthesia recovery period and postoperative hospitalization will be considered as secondary outcomes to comprehensively analyse the prognosis.

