There have been growing concerns about perioperative complications caused by IPH, and passive warming measures have been widely used in perioperative anaesthesia management. However, a single layer of the passive warming measure can only reduce skin heat loss by approximately 30%, and adding additional layers can only barely increase benefits (20). In contrast, active warming strategies are more effective, and the effects have been verified in adult patients (21). Active warming strategies generally include forced-air warming blankets (19, 22), infusion heating apparatuses (23), forced air warmers (24), body cavity lavage liquid heating (25), increasing operating room temperature (26), etc. In addition, some studies have pointed out that prewarming 30–60 min before the operation can effectively decrease the incidence of IPH by reducing the redistribution of core body temperature (27, 28). The aforementioned active warming measures have been partially applied in children's perioperative management (29), but few trials have systematically studied the effects of the series of active warming strategies in children. This multicentre, prospective, randomized controlled trial aims to verify the effect of perioperative active warming strategies in children, further reducing the incidence of IPH and improving the prognosis in paediatric patients.

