#### Other data to be recorded

2.7.3.

**Preoperative:** Baseline data, including demographic characteristics, basic vital signs, complications, and information related to anaesthesia and operation.

**Intraoperative:** Record vital signs and respiratory parameters every 10 min during anaesthesia, the type and dose of intraoperative medicines, intraoperative adverse events, total fluid volumes, and the durations of anaesthesia, surgery, and the recovery period.

**Postoperative:** The PACU stay period, medicine administration, Ramsay Sedation score and Wong-Baker Faces Scale scores recorded when the patient leaves the PACU.

**Follow-up:** Will be conducted during postoperative hospitalization and on the 30th day after the operation.

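### Incision infection (and, less importantly, major complications) is counted only until discharge although day-30 follow-up is planned, so later infections score as none and the window moves with length of stay, itself an outcome

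*Protocol article*

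**What the plan says.** All references are to the protocol article.

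- Section 2.7.2 (Secondary outcomes), item (6): "The incidence of incision infection during hospitalization".
- Same list, item (7): "The morbidity of major complications during postoperative hospitalization". The second note under the list repeats that limit when it names the components.
- Same list, item (8): "Length of stay and expenses".
- Same list, item (9): "All-cause mortality 30 days after the operation". This is the only outcome with a 30-day horizon.
- Section 2.7.3 (Other data to be recorded), on follow-up: "Will be conducted during postoperative hospitalization and on the 30th day after the operation".
- The Introduction ends its list of consequences of hypothermia, which also contains incision infection, with "internal environment disturbance (12), and prolonged length of stay".
- The Introduction gives the purpose as "further reducing the incidence of IPH and improving the prognosis in paediatric patients", and the abstract says of the secondary outcomes: "Multiple complications covering the anaesthesia recovery period and postoperative hospitalization will be considered as secondary outcomes to comprehensively analyse the prognosis".
- Section 2.5 (Randomization and blinding) keeps the follow-up researchers blind to allocation.

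Nothing in the article extends the count of infections or complications past discharge.

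**The concern.** Two separate consequences follow from ending the count at discharge.

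The first needs no difference between the arms. An infection that appears at home is recorded as absence of infection. The outcome then measures early infection in children still on the ward, and events that could inform the comparison are lost.

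The second concerns the comparison itself. Each child's window closes at discharge, which comes after randomization and which the intervention may influence. The trial's own rationale names both incision infection and longer stay as effects of hypothermia. If warming does shorten stay, Group A is watched for less time and shows fewer in-hospital infections even when the true risk is the same. Randomization does not protect against this, because the window is set by something that happens after it.

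At stake is whether a lower infection count in Group A could be read as fewer infections rather than less observation.

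**Working it through.** **What the text settles.** Items (6) and (7) end at discharge, item (8) is the quantity that determines when discharge occurs, item (9) runs to day 30, and follow-up on day 30 is planned. The window is stated, and stated consistently, so this is not a detail left to a fuller document.

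**What the text does not settle.** The document gives no infection rate, no onset times, no expected stay and no expected effect of warming on stay. There is no figure of the plan's own to reproduce. Everything below is an illustration under assumptions.

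**Share of infections seen by discharge on day L, F(L).**

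- Late-onset pattern (assumed): onset uniform over days 3 to 14, so F(L) = (L − 3)/11.
- Earlier-onset pattern (assumed): exponential onset cut off at day 30, so F(L) = (1 − e^(−kL))/(1 − e^(−30k)), with k = ln 2/m and m = 5, 7 or 10 days (the median before the cut-off).

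Example for m = 5: F(5) = (1 − 0.5)/(1 − 0.0156) = 0.508.

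Suppose the true risk is identical and every child stays 5 days in Group A and 6 days in Group C:

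| Assumed onset | F(5) | F(6) | F(6)/F(5) | Apparent A/C ratio |
|---|---|---|---|---|
| Uniform, days 3–14 | 2/11 = 18.2% | 3/11 = 27.3% | 1.50 | 0.67 |
| Exponential, m = 5 | 50.8% | 57.4% | 1.13 | 0.89 |
| Exponential, m = 7 | 41.2% | 47.2% | 1.15 | 0.87 |
| Exponential, m = 10 | 33.5% | 38.9% | 1.16 | 0.86 |

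Discharge on day 5 thus captures about 18% to 51%, and a one-day difference produces a spurious ratio of about 1.1 to 1.5. A fixed 30-day window gives 1.00 in every row, because both arms are observed equally long.

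**Information lost with equal stays.** Assume 30-day infection rates of 10% and 5%, and 160 evaluable children per arm (200 less 20% dropout). Two-sided power at 0.05 is about 40% with complete capture and about 22% if half the infections are seen. The 30-day count is more informative, but it does not make infection a well-powered outcome.

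**The case against.** The strongest reply is that this is a deliberate and consistent choice. The abstract and section 2.7.2 both limit complications to the hospital stay, the rule is the same in both arms, and ward records are better evidence than a parent's recollection. The abstract and Discussion put feasibility and thermal effect first. The primary outcome and sample size concern temperature only, and items (6) and (7) are two of nine secondary outcomes. All of that stands. It limits the importance of the point but does not remove it, because a common rule that ends at discharge still gives unequal windows when stays differ.

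Several stronger readings are tempting, and the documents do not support them:

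- *That the infection result will be biased towards Group A.* This requires warming to shorten stay. The Introduction makes that plausible, but no passage gives an expected effect. Dependence also runs the other way: a child with a developing infection would tend to be kept in, which the fixed stays in the illustration ignore.
- *That most infections will be missed because stays are short.* No stay is given. Section 2.3.1 includes neurosurgery and general surgery as well as otorhinolaryngologic and urological procedures, and outcome (5), next-morning temperature, implies at least one night.
- *That the spurious ratio is 1.5 or more.* That figure comes only from the uniform pattern, which allows no onset before day 3 and so inflates ratios for discharge shortly after it. Earlier onset gives 1.13 to 1.16.
- *That major complications need the same 30-day definition.* Several components, such as myocardial infarction, renal failure and unplanned intensive care transfer, are poorly ascertained by asking families, and the last is essentially an inpatient event.
- *That every family is already being asked suitable questions on day 30.* Section 2.7.3 says follow-up takes place then, but not how, or what is asked beyond what 30-day mortality implies.

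**Conclusion.** The point holds for outcome (6) and, to a lesser extent, for outcome (7). That post-discharge infections score as none follows from the definition alone. That the window varies with a post-randomization outcome also follows directly. A bias between the arms is conditional on warming changing length of stay; if it shortens stay, the direction favours Group A.

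The size is driven by assumptions. The capture of about 18% to 51% at day 5, and the ratio of about 1.1 to 1.5 for day 5 versus day 6, rest on assumed onset patterns and stays fixed within arm, and should not be quoted as estimates for this trial. The primary outcome is untouched. This is a worthwhile and inexpensive improvement to a secondary outcome, not a flaw that endangers the trial's main conclusion.

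**What to change.** - **Outcome (6):** redefine it as incision infection within 30 days of operation. Ascertain it with the same questions in both arms, in hospital and at the planned day-30 follow-up, by the blinded follow-up researchers. Report the in-hospital count as a descriptive split.
- **Outcome (7):** keep the in-hospital definition, label it as such wherever it is reported, and interpret it next to length of stay by arm. Optionally record at day 30 any readmission or treated complication as supplementary information.

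**Cost:** a changed line in the outcome list, a label for outcome (7), and a few added questions on the case report form at a follow-up already scheduled. This assumes that the day-30 follow-up reaches the family directly; if it does not, a short contact has to be added. The real downside is that post-discharge infections will be family-reported and less precise than ward records, which is why the in-hospital split should stay visible.
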